### Sample size, power, and statistical analysis

Based on preliminary assessments via electronic phenotyping in the EHR, we have identified a target sample of around 3000 patients (clustered within approximately 30 physicians at the two Penn Medicine sites) who may benefit from genetic testing for familial high-risk breast and ovarian cancer predisposition but have not done so. We calculated power conservatively by assuming correlations of 0 to 0.2, using PASS (Power and Sample Size, NCSS Software, Kaysville, UT). We found our sample gives us 80% power to detect at least a 5% improvement in our cumulative incidence of testing using a two-sided type 1 error rate of 5%, for planned comparisons between each stage in the sequence.

We will analyze the change in the incidence of scheduling counseling appointments across the three sequences (all time to event outcomes) using Cox regression, with variances adjusted for physician clustering. The models will contain time-varying binary predictor terms for each nudge, making adjustments for time in months, and fixed effects for site. We will control for type 1 error inflation by hierarchical testing, starting with the overall model significance, followed by the effect of each strategy. Once we have fitted the main effects model, we will test for each sequence and retain terms if significant (alpha = 5%). Variability in outcomes by sequence and moderators (particularly health equity variables) will be assessed using interaction terms within Cox regression models. We will fit an adjusted Cox regression model using the same approach described in the primary analysis. Covariates of interest available through the EHR will be added to the model, including patient-level (e.g., race), clinician-level (e.g., physician type), and practice-level (e.g., community vs. hospital-based) data.

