**Methods:**

Patients meeting eligibility for germline genetic testing for breast and ovarian cancer will be identified using electronic phenotyping algorithms. A pragmatic cohort study will test three sequential strategies to promote genetic testing, two directed at patients and one directed at clinicians, deployed in the electronic health record (EHR) for patients in OB-GYN clinics across a diverse academic medical center. We will use rapid cycle approaches informed by relevant clinician and patient experiences, health equity, and behavioral economics to optimize and de-risk our strategies and methods before trial initiation. Step 1 will send patients messages through the health system patient portal. For non-responders, step 2 will reach out to patients via text message. For non-responders, Step 3 will contact patients’ clinicians using a novel “pend and send” tool in the EHR. The primary implementation outcome is engagement with germline genetic testing for breast and ovarian cancer predisposition, defined as a scheduled genetic counseling appointment. Patient data collected through the EHR (e.g., race/ethnicity, geocoded address) will be examined as moderators of the impact of the strategies.

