### Study setting, population, and duration

This study will be conducted at gynecologic practices within two Penn Medicine centers: Penn Health for Women Radnor and the Helen O. Dickens Center for Women. These sites serve substantially different patient populations in terms of racial identity and insurance coverage, which may affect testing uptake. Most patients at Radnor are white (83.7% white, 6.5% Black, 3.0% Asian, 6.8% other/unknown), while the Dickens Center predominantly serves Black patients (73.7% Black, 18.9% white, 2.1% Asian, 5.3% other/unknown). Patients seen at these two sites since January 1, 2009 will be selected by an EHR-based algorithm established previously [71] using the following eligibility criteria: (1) serous ovarian cancer diagnosed more than two years prior to study contact; (2) breast cancer diagnosed at under 50 years of age more than two years prior to study contact; (3) triple-negative breast cancer diagnosed at any age more than two years prior to study contact; (4) unaffected individuals reporting a family history of ovarian cancer; (5) unaffected individuals reporting a family history of male breast cancer; and (6) at least two Penn Medicine appointments within the last three years. Utilizing electronic phenotyping in the EHR, participants who have previously received genetic counseling and testing will be excluded. Approximately, 3000 patients at these sites have been identified as eligible for genetic testing for familial high-risk breast and ovarian cancer based on these criteria, and these patients make up the target sample. The clinician sample (*N* = 30) will consist of gynecologists at participating practice sites associated with these patients. It is anticipated that the study will take approximately 18 months to complete. The study was approved by the University of Pennsylvania Institutional Review Board. The trial presents minimal risks to participants, and a waiver of informed consent was approved for all study aims.

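### The hierarchical testing rule does not secure the 5% type 1 error it claims: its gate includes site and time, and each strategy is then tested at an unsplit 5%

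*Protocol article*

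**What the plan says.** All of the rule stands in the Protocol article, section Sample size, power, and statistical analysis.

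- The model is a Cox regression: "The models will contain time-varying binary predictor terms for each nudge, making adjustments for time in months, and fixed effects for site".
- Multiplicity: "We will control for type 1 error inflation by hierarchical testing, starting with the overall model significance, followed by the effect of each strategy".
- After the main effects model is fitted, "we will test for each sequence and retain terms if significant", with alpha given as 5%.
- The power statement uses the same level: "using a two-sided type 1 error rate of 5%, for planned comparisons between each stage in the sequence".

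No order among the strategies, no rule that a failed test stops the next, and no split of alpha is given. The Abstract puts the number of strategies at three: "A pragmatic cohort study will test three sequential strategies to promote genetic testing, two directed at patients and one directed at clinicians". On the two clinics, Study setting, population, and duration says: "These sites serve substantially different patient populations in terms of racial identity and insurance coverage, which may affect testing uptake". The Study design section treats cumulative nudges as a time-varying covariate.

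**The concern.** A gate protects the tests behind it only if it tests the joint null hypothesis of those tests. Here it tests the whole model. A site difference, which the article itself gives reason to expect, or a time trend could make that model significant with no nudge effect, and the gate would then protect nothing.

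Even a gate on the nudges alone protects only against the case in which every nudge is null. With three separate nudge effects, once one is real the gate opens and the two null ones are each tested at the full 5%.

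Dropping terms is a further problem. With cumulative coding, removing a non-significant text-message term pools that step's person-time with the portal step's. The clinician term is then compared with a different reference, chosen after looking at the data.

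At stake is which steps are declared effective. The Discussion says that positive results may lead to large cluster randomized trials, so a false claim for one step could shape what is scaled up.

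**Working it through.** **Inputs from the article.** Two-sided 5% per test; three nudge terms; time and site in the same model; about 3000 patients under about 30 physicians. Correlations between nudge estimates, the size of any site effect and the number of events are not given, so they are assumed below.

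**The article's own figures.** The per-test level is as stated: 2 × (1 − Φ(1.96)) = 0.05. The power statement ("We found our sample gives us 80% power to detect at least a 5% improvement in our cumulative incidence of testing") can be neither reproduced nor refuted, because no baseline incidence is given. Over assumed baselines of 1% to 35%, power for a 5-point gain is 98% or more at correlation 0. It is 14% to 64% at correlation 0.2, read as clustering among 100 patients per physician. Nothing below depends on it.

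**Gate opened by site or time, no nudge effective.** With k true null contrasts, independent estimates and a gate that is always open, FWER = 1 − 0.95^k:

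- k = 2: 1 − 0.9025 = 9.75%
- k = 3: 1 − 0.857375 = 14.3%

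The gate does not always open, so the three-term case was simulated (400,000 draws per case) with a 5-df gate and correlations between estimates of −0.3 to 0.5. The site/time effect enters as a noncentrality. As a guide to scale, with an even split between sites and no allowance for clustering, noncentrality ≈ (events / 4) × (ln HR)². With 300 events, a site hazard ratio of 1.5 gives 75 × 0.164 = 12.3, and a ratio of 2.0 gives 75 × 0.480 = 36.0.

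| Site/time noncentrality | Gate opens | FWER, three null nudges |
|---|---|---|
| 10 | 68% | 11.3% to 12.8% |
| 30 | over 99% | 12.5% to 14.2% |

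The error stays near its limit even when the gate opens only two times in three, because a nudge that is significant by chance helps to open it. On a reading as comparisons between stages, the same two noncentralities give about 8% to 9% for two adjacent contrasts and 11% to 12% for three pairwise ones.

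**Gate restricted to the nudge terms.**

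| Situation | FWER |
|---|---|
| Three terms, all null | 4.0% to 4.8% |
| Three terms, one real (z shift 5 or 8) | 9.1% to 9.8% (formula 9.75%) |
| Three terms, one real (z shift 2.8) | 8.9% to 9.2% |
| Three terms, two real | 5.0% |
| Three stages, all equal | 4.2% to 5.0% |
| Three stages, one different | 4.7% to 5.0% |

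With only two contrasts, a nudge-only gate is enough. If both are null, the gate rejects 5% of the time; if one is real, a single null remains, tested at 5%.

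**After the fix.** With the gate followed by a fixed sequence that stops at the first failure, or by Holm, the highest simulated error in any case was 5.05% and 5.00% respectively. The simulation standard error is √(0.05 × 0.95 / 400,000) = 0.03 percentage points, so both agree with 5%.

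**The case against.** **Only two contrasts may exist.** The portal message goes to everyone at the outset, apart from patients without a portal account, and no un-nudged follow-up is described. If only stage-to-stage contrasts can be estimated, the 9% to 10% case disappears under a nudge-only gate. This stands as a limit on the size. It does not rescue the rule, because the written gate is not nudge-only, and with two contrasts a gate opened by site still allows up to 9.75%.

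**Site may not be in the gate.** The Study design section speaks of outcomes stratified by factors such as referral clinic, and a Cox model stratified by clinic has no site coefficient. But the analysis section specifies fixed effects for site and an adjustment for time, and it is the section that defines the model.

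**The word hierarchical implies a fixed order.** The design supplies a natural one (portal, text, clinician), and a fixed sequence with stopping would hold 5%. The detail might also be left to an analysis plan that is not shown. However, the only hierarchy the article states runs from the overall model to each strategy, and the next sentence tests each sequence at 5%. The objection is to that stated rule, not to missing detail.

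**The study is non-randomized and of minimal risk.** A false positive could be tested again in the later randomized trials. This argues for a lower priority, not for leaving the rule as it is.

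A reader might also infer that two primary outcomes, scheduling and completion, double the problem. The article names only scheduling in the Cox analysis and does not say that completion goes through this rule, so that is not supported.

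**Conclusion.** The rule as written does not deliver the control it claims. The firm part is the gate: a test of a model that contains site and time does not protect the nudge tests. If site or time opens it, the familywise error can reach 9.75% with two estimable contrasts or 14.3% with three. Both figures assume independent estimates and an open gate; correlation, or a gate that sometimes stays closed, lowers them. The site effects and event counts used to judge how often the gate opens are assumptions.

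The second part is conditional. About 9% to 10% applies under a nudge-only gate only if three separate nudge effects are tested and exactly one is real.

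A reader might infer that the error is always two to three times 5%. The documents do not support this. Under a nudge-only gate it stays near 5% if all nudges are null, if two of three are real, or if only two contrasts exist. This should be fixed, but it is not a fatal flaw.

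**What to change.** Replace the multiplicity sentences with a rule of this kind:

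1. Name the nudge contrasts that the design can estimate.
2. Gate on a joint cluster-robust Wald test of those nudge terms only, with site and time left out of the tested hypothesis.
3. If it is significant, test the contrasts in a stated fixed sequence at two-sided 5%, stopping at the first non-significant result, or use Holm.
4. Keep all nudge terms in the reported model whatever their p-values.

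This takes a few sentences and no new data. The cost is slightly lower power for later steps. With a fixed sequence in delivery order, a failed portal test would bar any claim for the clinician step, which the Background suggests may be the most influential. Holm avoids that, but tests the smallest of three p-values at 0.05 / 3 = 1.67%. The choice should be made before outcomes are analysed.

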## Methods

### Study design

This pragmatic study will use a non-randomized, sequential adaptive design to examine the effect of patient- and clinician-directed nudges informed by behavioral economics and delivered via the EHR for promoting the use of genetic testing for the identification of breast and ovarian cancer predisposition. Sequences are detailed in Fig. 1. Before the sequences begin, we will use electronic phenotyping procedures to identify a cohort of patients receiving care through two large OB-GYN clinics who are eligible for genetic testing for breast and ovarian cancer predisposition (based on information in the EHR), but who have no documentation of testing in the EHR [71]. Next, in the first sequence, all patients will be contacted via the MyPennMedicine (MPM) patient portal. Messages will be delivered twice, one week apart. The message will include direct information on patients’ cancer risk based on their genetic history, their ability to take action to address their risk, and how to contact the study team to schedule an appointment. Patients can reply directly to the MPM message, call the Cancer Risk Evaluation Program (CREP), or use an outreach-specific email address. Patients who do not engage with the CREP within three weeks will receive the next adaptive sequence, a direct text message targeting omission bias to promote breast and ovarian cancer genetic testing. Again, patients will receive two text messages, a week apart, and will be given three weeks to schedule an appointment. The text message program will be conducted through Penn Way to Health, an evidence-based patient engagement platform [72, 73]. Finally, if patients do not engage with the genetics team, their clinicians will receive an EHR-based nudge targeting status quo bias using the “pend and send” functionality with a pended genetics consult order as a default. A final 6-month observation period will track the scheduling of genetic counseling and genetic testing results for breast and ovarian cancer predisposition following clinician strategy delivery. Patient characteristics (e.g., age, race/ethnicity, nature of genetic risk) will be ascertained from the EHR and explored as moderators of the effectiveness of each sequence to promote genetic testing. This sequential adaptive design will allow for comparisons of which strategies work best across clinics and subgroups of patients.

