**Fig. 1 Fig1:**
[figure not shown]
Study design

The primary implementation outcomes will be rates of scheduling and completion of genetic counseling appointments, stratified by factors such as referral clinic and diagnosis, with cumulative nudges representing a time-varying covariate. Decisions to undergo genetic testing in a timely manner are dependent on several factors, including patient preference. Additionally, a counseling discussion can alleviate some patient concerns about testing and may be more acceptable to patients. As such, scheduling the initial genetic counseling appointment was chosen as a primary outcome in addition to appointment completion. Process outcomes will include open rates for the two patient-directed strategies and the proportion of pended orders signed by referring clinicians. We will compare the number of appointments scheduled after each sequence and across patient-level characteristics (e.g., race and ethnicity) and site.

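### The moderator-by-nudge interactions measure only how a group gap changes between steps, so they cannot show whether each strategy works equally well across groups

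*Protocol article*

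**What the plan says.** **Aim.** The Study design section says patient characteristics will be "explored as moderators of the effectiveness of each sequence to promote genetic testing". The Abstract states the same purpose.

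**Model.** In the section on sample size, power and statistical analysis: "The models will contain time-varying binary predictor terms for each nudge, making adjustments for time in months, and fixed effects for site". The Study design section, after Fig. 1, describes the coding: "with cumulative nudges representing a time-varying covariate". Moderators are handled in the same model: "Variability in outcomes by sequence and moderators (particularly health equity variables) will be assessed using interaction terms within Cox regression models". An adjusted Cox model then adds covariates, race among them.

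**Timetable.** "Next, in the first sequence, all patients will be contacted via the MyPennMedicine (MPM) patient portal". Then: "Patients who do not engage with the CREP within three weeks will receive the next adaptive sequence". At the text step patients again "will be given three weeks to schedule an appointment", after which the clinician nudge follows. The Patient nudges section adds an exception: patients without a portal account go to the text step.

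**Other looks at the groups.** The Study design section also plans to compare appointments after each step across race, ethnicity and site. The Measures section plans rates stratified by the moderators.

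**The concern.** An interaction between a moderator and a treatment indicator shows moderation of that treatment's effect only if the indicator varies, that is, if there is time at risk both with and without the treatment. Here the portal indicator does not vary for patients on the standard timetable. The later indicators do vary, but the contrast is with time under an earlier nudge, not with no nudge.

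The quantity estimated is therefore the change in the group gap from one step to another. The stated question is whether each strategy works equally well across groups. The two can disagree in both directions, and the article singles out health equity variables for this analysis. The practical risk is that a gap found only at the portal step is reported as the text or clinician nudge working better in Black patients.

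**Working it through.** The article gives no power figure for the moderator test. Its 80% concerns comparisons between stages, and has no bearing here.

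**1. What the terms estimate.** Take race as the moderator. Let P, T and C be the portal, text and clinician indicators, each staying at 1 once switched on. The race part of the log hazard is

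r·race + a·race·P + b·race·T + c·race·C.

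On the standard timetable P = 1 from day 0, T = 1 from about week 3 and C = 1 from about week 6. The race log hazard ratio is then:

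- portal step: r + a
- text step: r + a + b
- clinician step: r + a + b + c

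Only the sum r + a can be estimated. The term b is the change in the gap from portal to text, and b + c is the change from portal to clinician step. Under cumulative coding c alone is the further change after the text step. If each indicator were switched off at the next step, b and c would each be measured directly from the portal step.

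**2. Rank check.** The information matrix for seven terms (three nudges, race, three interactions) was computed for simulated patients who all follow the timetable. Its rank is 3. Race and race by portal carry identical information (177.693 each), and the three nudge main effects carry none. When an assumed 15% and 22% of the two race groups have no account and start texts on day 0, the rank becomes 7. All separation of a from r then rests on that self-selected group.

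**3. Gap in the portal step only.** Inputs: about 3000 patients (article); race mix from the Study setting section with two equal-size sites (assumed), so the Black share is (73.7 + 6.5)/2 = 40.1%, or about 1200 against 1800; race hazard ratios 0.5, 1, 1 (assumed). A hand approximation for the portal-to-text change uses variance = sum of 1/events:

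| Uptake per step (assumed) | Portal events, others / Black | Text events, others / Black | SE | z = ln 2 / SE | Power |
|---|---|---|---|---|---|
| 5% | 90 / 30.4 | 85.5 / 58.5 | 0.270 | 2.57 | 73% |
| 8% | 144 / 49.0 | 132.5 / 92.1 | 0.214 | 3.24 | 90% |

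Portal events among Black patients are 1200 × (1 − 0.95^0.5) = 30.4 and 1200 × (1 − 0.92^0.5) = 49.0. Power is Φ(z − 1.96). Simulation of 400 trials per scenario, with site in the model and a 2-df interaction test, gave 77% and 93%. The test thus rejects often although response in steps 2 and 3 is equal across groups.

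**4. Constant gap.** With a hazard ratio of 0.6 at every step (40% Black, three uptake patterns from 5/5/5% to 15/10/15%, no clustering, 1000 runs each), the interaction test rejects in 4.4% to 5.3%. A single race term rejects in 99% to 100%, and a 3-df test of the by-step race effects in 98% to 100%. In the 400-trial simulation with site and 30 physicians, the interaction test rejected in about 5% with model-based variance and 9% to 11% with cluster-robust variance.

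**5. Gap that changes.** With ratios 0.4, 0.6 and 0.9, the interaction test rejects in 72% to 99%. It works well for the question it does answer.

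**The case against.** Much of the opposing case stands.

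- **The interaction answers a question the article asks.** The Background chose the design to learn the relative effects of the strategies and expects texting to reduce inequities tied to portal access. Whether the gap shrinks from portal to text is that question, and rejecting under 0.5, 1, 1 is then a correct result. This stands. The trouble lies only in reading the result as a statement about the later step on its own.
- **A constant gap would not go unseen.** A reader might infer that it would be passed off as no moderation. The document does not support that. No rule equates a null interaction with equity, and the race covariate, the stratified rates and the by-race comparisons would all show the gap.
- **The rejection rates of 5% and 98% to 100% are not a power failure.** They belong to two hypotheses: no change in the gap, and no gap. A constant gap need not be moderation. The Background reports an existing racial disparity in testing in this health system, and a 3-df test would reject on that alone.
- **Not every nudge term is on from day 0 for everyone.** Only the portal term is, and patients without an account are excepted.
- **Parameterisation may be settled in a fuller document.** Without a race main effect, three race-by-nudge terms tested jointly would pick up a constant gap. But that would still be a test of any gap. No parameterisation supplies the missing un-nudged reference.

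**Conclusion.** The concern holds in a limited form. For patients on the standard timetable, moderation of the portal nudge cannot be separated from the moderator's own effect. The remaining interactions estimate change in the gap after the portal step. They do not show whether each strategy works equally well across groups, which is the stated aim.

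This follows from the described timetable and does not depend on the simulated rates. The sizes do: 77% to 93% rejection for a portal-only gap assumes a hazard ratio of 0.5, uptake of 5% to 8% per step and sites of equal size. Patients without an account soften the algebra, but offer only a self-selected comparison. The moderators are exploratory and other planned summaries show the gaps, so this is a matter of what is reported and how it is labelled. It does not make the equity analysis unusable.

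**What to change.** In the statistical analysis section:

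1. For each step, report the moderator hazard ratio within that step (main effect plus the interactions in force) and the difference in proportion scheduled among patients entering the step, each with a 95% confidence interval. Make these the main equity result.
2. Label the interactions as change in the gap relative to the portal step, and state the coding so that a reader knows which step each coefficient is compared with. Do not report a moderator-by-portal term as moderation of the portal nudge.
3. Describe within-step gaps as differences in response to outreach that may include pre-existing disparity, not as causal differences in nudge effect. If a joint 3-df test is used, call it a test of any gap.

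The cost is a few sentences and linear combinations of coefficients from the model already planned; no new data are needed. The small downside is a weaker claim about moderation of nudge effectiveness.

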### Measures

The primary outcomes are the rates of contacted patients who schedule and complete a genetic counseling appointment within six months after each sequential step, collected via the EHR. As process measures, we will evaluate the proportion of patients who open MPM messages or respond to text messages within one month of receiving them, as well as the proportion of pended orders that clinicians sign within one month to refer patients for a genetics consult. Potential moderating variables will also be collected, including patient demographics (age, race, ethnicity, diagnosis, health insurance, address, and geocoded area as a proxy for neighborhood-level socioeconomic status), clinician data (practice site, years in practice), and practice-level information (community vs. hospital-based setting, urban vs. non-urban location, health insurance mix). These data will be used to describe the sample of participating patients and clinicians and to identify factors that may influence strategy effectiveness. Genetic counseling and testing rates will be evaluated after being stratified by these factors.

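### With two sites and a site fixed effect, practice-level covariates are aliased with site, and a race-by-step interaction needs site-by-step in the same model

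*Protocol article*

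**What the plan says.** All references are to the Methods of the protocol article.

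- **Sites.** Study setting, population, and duration: "This study will be conducted at gynecologic practices within two Penn Medicine centers". Sample size, power, and statistical analysis: the target sample of about 3000 patients is "clustered within approximately 30 physicians at the two Penn Medicine sites".
- **Primary model.** Cox regression with time-varying binary terms for each nudge, "making adjustments for time in months, and fixed effects for site".
- **Adjusted model.** "We will fit an adjusted Cox regression model using the same approach described in the primary analysis", with patient-level covariates such as race and then "clinician-level (e.g., physician type), and practice-level (e.g., community vs. hospital-based) data".
- **Practice-level variables.** Measures lists them among the potential moderators as "practice-level information (community vs. hospital-based setting, urban vs. non-urban location, health insurance mix").
- **Clinicians.** The 30 clinicians "will consist of gynecologists at participating practice sites associated with these patients". The clinician data listed in Measures are practice site and years in practice; physician type is not among them.
- **Moderators.** They are tested by interaction terms in the Cox models, with emphasis on health-equity variables.
- **Race by site.** "Most patients at Radnor are white (83.7% white, 6.5% Black, 3.0% Asian, 6.8% other/unknown"). The other center is 73.7% Black, 18.9% white, 2.1% Asian and 5.3% other or unknown.

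**The concern.** Two sites supply exactly one between-site comparison, and the site fixed effect uses it. The plan nevertheless names three practice-level variables and intends to use them as covariates and moderators. Each can only restate the difference between the two clinics.

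Race raises a related but weaker problem. Because the clinics differ so much in racial mix, a difference between clinics in how well a nudge works can appear as a difference between racial groups. A site main effect does not prevent this: it adjusts the baseline hazard, not the effect of each step.

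Moderation, particularly by equity factors, is a stated purpose of the study, and the Discussion foresees scaling to other sites. If a clinic difference were reported as an effect of setting, location, insurance mix or race, it would point that later work at the wrong cause.

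**Working it through.** The only computed figure in the statistical section is the 80% power statement. This point does not depend on it. It also cannot be reproduced uniquely, because neither the baseline incidence nor the type of correlation assumed is given.

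**1. Rank of the planned model**

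Inputs from the article: 2 sites, about 30 physicians, about 3000 patients, 3 steps. An intercept column stands in for the Cox baseline hazard, and two columns carry the text and clinician contrasts against the portal step. Practice-level variables take one value per site. The values used are arbitrary, since any two distinct values give the same rank.

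| Model | Columns | Rank |
|---|---|---|
| Intercept, 2 nudge contrasts, site | 4 | 4 |
| + setting | 5 | 4 |
| + setting, urban location, insurance mix | 7 | 4 |
| + nudge × setting (no nudge × site) | 6 | 6 |
| + nudge × setting and nudge × urban location | 8 | 6 |
| + nudge × setting and nudge × site | 8 | 6 |
| + physician type, if constant | 5 | 4 |
| + years in practice | 5 | 5 |
| + race | 5 | 5 |
| + race and nudge × race | 7 | 7 |

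Rows 2 and 3 show that no practice-level main effect can be estimated beside site, whatever the sample size. Rows 4 to 6 show that one nudge-by-setting interaction can be fitted, but that it is the same term as nudge-by-site and cannot be separated from nudge-by-urban-location. The last two rows show that race and its interaction are estimable.

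**2. Association of race with site (Black versus white)**

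Inputs: Radnor 6.5% Black and 83.7% white; the other center 73.7% Black and 18.9% white. The site split is not given, so it is varied. The cohort is assumed to mirror the clinic mix.

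- P(Black | other center) − P(Black | Radnor) = 0.737/0.926 − 0.065/0.902 = 0.796 − 0.072 = 0.724, whatever the split.
- At an even split, P(other center | Black) − P(other center | white) = 0.737/0.802 − 0.189/1.026 = 0.919 − 0.184 = 0.735.
- φ = √(0.724 × 0.735) = 0.729. Variance inflation = 1/(1 − φ²) = 2.14.

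| Share of patients at Radnor | φ | Variance inflation | Standard error × | Share of site-by-step loaded on race-by-step |
|---|---|---|---|---|
| 30% | 0.669 | 1.81 | 1.35 | 62% |
| 50% | 0.729 | 2.14 | 1.46 | 73% |
| 70% | 0.732 | 2.16 | 1.47 | 74% |

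The last column is the difference P(other center | Black) − P(other center | white). In a linear approximation this is the fraction of an omitted site-by-step effect that passes into race-by-step. Comparing Black patients with all others instead gives variance inflation of 1.6 to 1.9 over the same range of splits.

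**3. Information on race within site**

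At an even split of 3000, Radnor has 1500 × 0.065 ≈ 98 Black and 1500 × 0.837 ≈ 1256 white patients. The other center has 1500 × 0.737 ≈ 1106 Black and 1500 × 0.189 ≈ 284 white patients. The smaller group at each site limits the within-site contrast, but both contrasts exist.

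**The case against.** **The moderator analysis is not defeated.** A reader might infer that practice-level moderators cannot be fitted at all, or that the equity models fail as a whole. Neither is supported. One nudge-by-setting interaction is full rank beside the site main effect; the fault is attribution, not estimability. Most equity moderators in Measures (race, ethnicity, insurance, address, geocoded area) are recorded per patient and can be estimated. This stands.

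**Physician type may vary.** A reader might take it as certain that this covariate is constant. It is if it means specialty, since all clinicians are gynecologists. But the article does not define it, and training level or role could differ. A constant covariate would also drop out of the partial likelihood without biasing anything else. What remains is an undefined covariate that is missing from the list of clinician data.

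**Site differences are already in view.** Measures lists practice site among the potential moderators, and Study design plans comparisons across clinics as well as patient groups. So it would be wrong to say that the plan ignores site heterogeneity. But nothing says that site-by-step enters the same model as race-by-step, and separate models would not protect the race estimate.

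**The overlap is partial.** Variance inflation near 2 is not failure, and it is calculated for race given site, not for the interaction itself. That is fair, and it is why the race interaction can be kept once site-by-step stands beside it.

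**Software would flag the aliased term, and moderators are exploratory.** Both are true. They limit the harm but do not make the named terms meaningful. Practice-level data may still properly describe the sample.

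**Conclusion.** The point holds for practice-level terms without any numerical assumption beyond two sites and variables measured at site level. Their main effects have zero degrees of freedom beside the site term, and as moderators all three reduce to the single nudge-by-site contrast.

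The race part is conditional. If race-by-step is fitted without site-by-step, most of any site difference in nudge effect (about 62% to 74%) would be read as a race difference. That range assumes that the cohort mirrors the stated clinic mix, a 30:70 to 70:30 split, and a linear approximation. The article does not say that the terms would be fitted apart; it leaves this open.

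The primary main-effects nudge analysis is unaffected. The change should be made because it alters what the moderator analysis can conclude and costs little.

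**What to change.** 1. Remove setting, urban location and insurance mix as separate model terms. Report one site contrast and one site-by-nudge contrast, labelled as site only. Keep the practice-level data for describing the sample.
2. For each patient-level equity moderator, fit moderator-by-step and site-by-step in the same model, and report race-specific results by site. Patient-level insurance and geocoded area, already to be collected, can address the questions that insurance mix and location were meant to answer.
3. Define physician type and add it to the clinician data, or replace it with years in practice, which is already listed.

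Possible wording: *Site enters as a fixed effect and, in moderator models, as a site-by-step interaction. With two sites, no practice characteristic will be modelled separately, and site differences will not be attributed to a particular characteristic.*

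The cost is precision. The within-site race interaction will have wider intervals than a pooled one; as a guide, the standard error for race given site rises by about 35% to 47% under the assumptions above. No further data are needed unless physician type is kept.
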